**a. Overview of Study Design**

As part of implementation of the pilot FAM-CARE program in Swaziland, health care facility clusters have been randomized to initiate the pilot FAM-CARE program (two health care facility clusters) or continue to provide the current standard of HIV care with separate pediatric and adult HIV clinics (two health care facility clusters). Our study will be an evaluation of this pilot program. Our program evaluation will enroll and follow a prospective cohort of HIV-positive children from selected FAM-CARE sites and control sites to assess the effects of the FAM-CARE program on retention and viral suppression in HIV-positive children on ART. Clinical care for the children is provided through the program and not the study; the study is to evaluate the effect of the program on pediatric viral suppression and retention in care. The FAM-CARE program (described below) is being implemented under the USAID-funded AIDSFree project; no aspects of this care program will be supported through SOAR funding. The SOAR funding is solely being used to support the research evaluation of the program’s effect on pediatric viral suppression and retention.

1. **Study Relationships/Related Project**

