The primary study endpoints are the proportion of children on ART with viral suppression (defined as HIV RNA below the level of assay detection) and the proportion with HIV RNA >1,000 copies/mL at 18 months. The tables below show the minimum number of children receiving ART needed to demonstrate significant (0.05) effects of the FAM-CARE program on viral suppression and HIV RNA >1,000 copies/mL compared to control facility care, assuming different viral suppression and HIV RNA >1,000 copies/mL rates in the control group.

**Table 3** (viral suppression) shows the minimum sample size per arm and overall needed to demonstrate a significant FAM-CARE program effect with 80% power at 5% significance levels, assuming different levels of viral suppression in children on ART from control facilities (ranging between 65-85% suppression) and different levels of improvement that could be observed in children in FAM-CARE program sites compared to control sites. With 398 HIV-positive children receiving ART from unique families, we will have 80% power to detect at least a 10% increase in viral suppression with FAM-CARE, assuming a viral suppression rate between 65% and 80% in control children on ART.

**Table 3.** Sample size estimates for detecting FAM-CARE effects on viral suppression rates

| % Viral Suppression in Control | Minimum Effect of FAM-CARE | % Viral Suppression in FAM-CARE Sites | Alpha | Power | Sample size/ arm | Total sample size | Adjusted for 10% LTFU |
| --- | --- | --- | --- | --- | --- | --- | --- |
| .65 | .15 | .80 | .05 | 80% | 138 | 276 | 308 |
| .65 | .20 | .85 | .05 | 80% | 73 | 146 | 164 |
| .65 | .25 | .90 | .05 | 80% | 43 | 86 | 96 |
| .70 | .15 | .85 | .05 | 80% | 121 | 242 | 270 |
| .70 | .20 | .90 | .05 | 80% | 62 | 124 | 138 |
| .75 | .15 | .90 | .05 | 80% | 100 | 200 | 224 |
| .80 | .10 | .90 | .05 | 80% | 199 | 398 | 444 |
| .85 | .05 | .90 | .05 | 80% | 686 | 1372 | 1526 |

**Table 4** (HIV RNA >1,000 copies/mL) shows the minimum number of children required to detect at least a 5%, 10%, or 15% improvement with FAM-CARE care sites compared to control sites, with 80% power at 0.05 significance level, assuming different HIV RNA >1,000 copies/mL rates in control children (ranging from 10-30%).

**Table 4:** Sample size estimates for detecting FAM-CARE effects on HIV RNA >1,000 c/mL

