| % HIV RNA >1,000 c/mL in Control | Minimum Effect of FAM-CARE | % HIV RNA >1,000 c/mL in FAM-CARE Sites | Alpha | Power | Sample size/ arm | Total sample size | Adjusted for 10% LTFP |
| --- | --- | --- | --- | --- | --- | --- | --- |
| .10 | -.05 | .05 | .05 | 80% | 435 | 870 | 968 |
| .15 | -.05 | .10 | .05 | 80% | 686 | 1372 | 1526 |
| .15 | -.10 | .05 | .05 | 80% | 141 | 282 | 314 |
| .20 | -.05 | .15 | .05 | 80% | 906 | 1812 | 2014 |
| .20 | -.10 | .10 | .05 | 80% | 199 | 398 | 444 |
| .20 | -.15 | .05 | .05 | 80% | 76 | 152 | 170 |
| .25 | -.10 | .15 | .05 | 80% | 250 | 500 | 556 |
| .25 | -.15 | .10 | .05 | 80% | 100 | 200 | 244 |
| .30 | -.10 | .20 | .05 | 80% | 294 | 588 | 654 |
| .30 | -.15 | .15 | .05 | 80% | 121 | 242 | 270 |

We have adjusted the effective sample size to account for a possible 10% loss to follow up over the 18-month study period. Our estimation assumes enrolment of one HIV-positive child on ART per household and that there is no correlation of children’s viral load outcomes within facilities.

Assuming 10% loss to follow-up, we plan to enroll 444 HIV-positive children receiving ART from unique family units into the study over 12 months. With this sample size, we have power to detect a minimum of 10% increase from an estimated proportion of viral suppression of 80% in the control sites to 90% in the FAM-CARE sites or 15% increase in viral suppression with FAM-CARE if control rate of suppression is 75% or lower (Table 3 highlighted rows) and a minimum reduction in HIV RNA >1,000 copies/mL rates from 20% in the control sites to 10% in the FAM-CARE sites or from 15% in the control sites to 5% in the FAM-CARE sites (Table 4 highlighted rows).

*Study sampling procedures*

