However, there is potential correlation of viral outcomes of children from the same family as well as children from the same facility, thereby violating the assumption of independence required for validity of the chi-square test. We propose to use multilevel generalized linear models to account for the potential intra-cluster correlation due to family unit and facility. In addition, we will adjust for potential confounding that may arise due to imbalances in children’s characteristics between study arms.

b) If the FAM-CARE program decline rate is substantial (>10%) and baseline characteristics of children differ significantly between those who accept FAM-CARE and those who decline, we propose to use the propensity score method to match and compare FAM-CARE and non- FAM-CARE participants. Using data from the FAM-CARE sites, we will estimate the probability of accepting FAM-CARE program given the baseline children and family characteristics. Using special matching algorithms, we will develop a statistical control group that will be compared with the FAM-CARE group. Regression modeling will be used to estimate the effect of the FAM-CARE group compared to the control group.

c) Finally, we will perform an intent-to-treat analysis in which all children at facilities offering the FAM-CARE program will be compared to all children at facilities without FAM-CARE program.

To answer primary aim 2, we will use the same statistical approach described for specific aim 1 above.

To answer secondary objectives 1 and 3, the analysis for the primary objective described above will be repeated using the appropriate outcomes.

To identify factors associated with viral suppression and HIV RNA >1,000 copies/mL (secondary objective 2), we propose to use multilevel logistic regression models to estimate the association between viral suppression and putative factors in each study arm. Examples of factors that might be evaluated include age and gender of child, when ART initiated and ART regimen, serious illness or hospitalization, timeliness of pharmacy drug pick-up, school attendance, family size, number of other HIV-positive individuals in family, HIV treatment and clinical status of other HIV-positive family members, disclosure of HIV status within family.

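### The 80% power for the 10-point effect that sets the sample size holds only with no within-facility or within-cluster correlation, although four whole clusters were allocated and the analysis section plans for such correlation

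*Protocol*

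**What the plan says.** **Allocation.** Overview of Study Design: "health care facility clusters have been randomized to initiate the pilot FAM-CARE program (two health care facility clusters") while the other two continue standard care. Figure 1 shows the allocation stratified by hospital or health-centre cluster, so each arm holds one of each. Enrolment is at eight facilities, four per arm.

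**Sample size.** The Sample size estimation section gives tables "with 80% power at 5% significance levels". Two rows set the target:
- Table 3, viral suppression: "80 | .10 | .90 | .05 | 80% | 199 | 398 | 444"
- Table 4, HIV RNA above 1,000 copies/mL: "20 | -.10 | .10 | .05 | 80% | 199 | 398 | 444"

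The text attaches the power to 398 children: "we will have 80% power to detect at least a 10% increase in viral suppression with FAM-CARE". The only inflation is for dropout: "Assuming 10% loss to follow-up, we plan to enroll 444 HIV-positive children receiving ART from unique family units". Below Table 4 the protocol states that the estimate takes one child on ART per household and that "there is no correlation of children’s viral load outcomes within facilities". The next paragraph says that 444 children give power for the 10-point effects, and for a 15-point gain in suppression if the control rate is 75% or lower.

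**Analysis.** The Statistical Analysis Plan section first describes a chi-square test. It then says that there is "potential correlation of viral outcomes of children from the same family as well as children from the same facility", that this violates the independence the test needs, and that multilevel generalized linear models with family and facility will be used.

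**The concern.** The sample size and the analysis rest on opposite premises. Sizing uses the formula for independently allocated children. The analysis treats children in the same facility as possibly correlated. If they are, the multilevel analysis carries less information than 199 independent children per arm, and the 80% is not achieved. The protocol has no ICC, no design effect and no allowance for there being only two randomised clusters per arm.

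The stake is how a non-significant result would be read. The Summary says that the sponsor will work with the Ministry of Health on wider roll-out if the programme is found effective. A reader who trusts the stated 80% could take a non-significant 18-month comparison as fair evidence that a 10-point gain is absent, when the chance of detecting that gain may have been much lower.

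**Working it through.** **Inputs.** From the protocol: two-sided 5% (sidedness is not stated, but two-sided reproduces the tables), 80% power, 80% against 90%, 199 per arm, 10% loss to follow-up, 2 clusters or 4 facilities per arm. Assumed, because the protocol gives none: ICC from 0.001 to 0.05, and equal cluster sizes.

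**1. Reproduce the stated figure (ICC = 0).**
n = [1.960·√(2p̄q̄) + 0.842·√(p₁q₁ + p₂q₂)]² / d²
With p̄ = 0.85: 2p̄q̄ = 0.255. With p₁ = 0.80 and p₂ = 0.90: p₁q₁ + p₂q₂ = 0.25. d = 0.10.
n = (0.990 + 0.421)² / 0.01 = 199 per arm. Then 199/0.9 = 221.1, rounded up to 222, so 444 in total. The formula returns 80.0% power at n = 199. The 20% against 10% row has the same variances, so everything below applies to it as well.

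**2. Add clustering.** With k units per arm and m = 199/k children per unit, DE = 1 + (m − 1)·ICC and n_eff = 199/DE.
Power = Φ[(0.10·√n_eff − 1.960·√0.255) / √0.25]

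Example, ICC 0.01:
- Cluster (m = 99.5): DE = 1 + 98.5 × 0.01 = 1.985, n_eff = 100.3, power = Φ(0.02) = 51%.
- Facility (m = 49.75): DE = 1.4875, n_eff = 133.8, power = Φ(0.33) = 63%.

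| Assumed ICC | Power, cluster as unit (2 per arm) | Power, facility as unit (4 per arm) |
|---|---|---|
| 0 | 80% | 80% |
| 0.001 | 76% | 78% |
| 0.005 | 63% | 71% |
| 0.01 | 51% | 63% |
| 0.02 | 37% | 51% |
| 0.05 | 21% | 32% |

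**3. Small number of units.** Step 2 uses a normal reference. A t reference on 2(k − 1) degrees of freedom with noncentrality 0.10/√(0.25/n_eff), which is 2.82 at ICC 0, gives:
- 2 df (critical value 4.30): 36% at ICC 0, 22% at 0.01, 11% at 0.05.
- 6 df (critical value 2.45): 66% at ICC 0, 49% at 0.01, 25% at 0.05.

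These show sensitivity to the number of units. They are not the planned analysis.

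**4. Larger effects.** For 75% against 90% at 199 per arm, the normal approximation gives 98% at ICC 0. By cluster it gives 80% at ICC 0.01, 63% at 0.02 and 36% at 0.05. By facility it gives 90%, 80% and 57%. On 2 df at ICC 0.01 it is 36%.

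**5. Can more children help?** As m grows, n_eff per arm approaches k/ICC. With k = 2 and ICC 0.02 the ceiling is 2/0.02 = 100 per arm, or 51% power. At ICC 0.01 the ceiling is 200, so 80% is reached only at the limit. At ICC 0.005 the ceiling is 400, and about 197 analysable children per cluster would reach 80% by the normal approximation.

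**The case against.** The strongest reply is that nothing is hidden. The assumption is printed just before the power statement for 444 children, and the arithmetic is correct. The analysis section speaks of potential correlation, not established correlation, and with no ICC in the protocol the true power is unknown. If the ICC were 0.001, the loss is only 2 to 4 points. The four clusters are those of the region and were allocated by the programme, so the evaluation could not simply add more.

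Much of this stands. The fault is a premise that the design and analysis do not support, not a miscalculation. Disclosure does not settle it, because the power statements that follow carry no range and the same protocol later plans for the correlation it set to zero.

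Some stronger readings are tempting, and the documents do not support them:
- *The claimed power does not exist at all.* That depends on an unknown ICC, and the 15-point claims keep useful reserve at small ICCs.
- *More children could never help.* By the normal approximation this holds for 80% power at an ICC of about 0.01 or more with two clusters per arm, not below.
- *The trial can never reach p < 0.05.* A stratified randomisation test has 2 × 2 = 4 possible assignments and so a smallest two-sided p-value of 0.5, but no such test is planned. Nor is a 2-df t test.
- *Clustering will be ignored in the analysis.* The protocol moves from the chi-square test to a multilevel model for this reason.

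Equal unit sizes are a simplification. Table 2 lists 36 children on ART at the smallest study facility and 318 at the largest. Unequal sizes would normally lower power further, so this does not rescue the claim.

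**Conclusion.** The point holds for the 10-point effect that sets the sample size. The stated 80% is correct only with no correlation within facilities and clusters. It drops to 76% (cluster) or 78% (facility) at an assumed ICC of 0.001, and to 21% or 32% at 0.05. Respecting the few units lowers it further: 36% on 2 df or 66% on 6 df, even at ICC 0. The 15-point suppression claim is sturdier but also falls short at larger ICCs. The results rest on an assumed ICC range, equal unit sizes and one child per family. No single true power can be given. What can be said is that the protocol's unqualified figure is the best case of that range and conflicts with its own analysis section.

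**What to change.** Keep 444 children and the planned 5% test. In Sample size estimation:

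1. Replace the no-correlation assumption and the 80% statements, for both endpoints, with a power table over a stated ICC range, for example 0.001 to 0.05. Give the source of any ICC used.
2. Build in a design effect, say whether the unit is the randomised cluster or the facility, and allow for the small number of units.
3. Show the 10-point and 15-point effects separately.
4. State that a non-significant result does not come from an 80%-powered comparison, and that the effect estimate will be reported with a confidence interval that accounts for clustering.

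The cost is protocol wording and a less favourable power statement. There are no extra children, visits or sites. Giving up the 5% test in favour of estimation alone is a defensible option but is not required.

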SOAR partner Elizabeth Glaser Pediatric AIDS Foundation (EGPAF) proposes to leverage existing and planned service delivery platforms in Swaziland to evaluate a model of care to improve pediatric retention and ART adherence. In the family-centered care (FAM-CARE) program, after identification of HIV infection in a child, active HIV testing of all family members is conducted and all HIV-positive family members are seen together as a unit and receive their care together. EGPAF-Swaziland is in the process of establishing a FAM-CARE service delivery program in selected health facilities in the Hhohho region of Swaziland, and roll-out of these services will provide a platform for this study. Viral load monitoring is in process of national roll-out in Swaziland. The planned study is an implementation science study to evaluate the implementation of the FAM-CARE program in Swaziland and its effect on viral suppression and retention in children living with HIV.

The proposed study will evaluate the effect of implementing a FAM-CARE program on viral suppression and retention in children through enrollment of a prospective cohort of HIV-positive children and their caregivers at sites implementing the FAM-CARE program and control sites continuing the current standard of care. The study will be conducted in four “clusters” of facilities (2 hospitals and 2 health centers and their filter clinics) in the Hhohho region of Swaziland. Two facility “clusters” (one hospital and one health center, with their filter clinics) will be randomized to initiate the FAM-CARE program with viral load monitoring and two “clusters” (one hospital and one health center, with their filter clinics) will be control standard-of care sites. A prospective cohort of HIV-positive children and their caregivers will be followed in the FAM-CARE program sites and control sites. Each child will be followed for 18 months following enrollment. The primary objective is to evaluate the effect of the FAM-CARE program on the rates of viral suppression and retention in care, comparing rates of viral suppression and retention in children enrolled in FAM-CARE vs control sites. The study will also evaluate factors associated with viral suppression and retention (including family demographic characteristics), and conduct qualitative interviews to assess the acceptability of the FAM-CARE program by caregivers and health care providers in the intervention sites.

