**ii. Research Protocol/Methods**

1. ***Study Procedures***

After obtaining written informed consent from the caregiver and verbal informed assent from children < 12 years, eligible HIV-positive children will be enrolled in the study into the FAM-CARE or control arm depending on the facility h/she attends. An enrollment visit will be conducted, during which caregivers will be interviewed to collect demographic, medical and HIV-related information about the child. Clinical/laboratory data will be abstracted from clinic medical records. The caregiver will be interviewed regarding HIV infection status of other family members and clinical/treatment history obtained for other HIV-positive family members by interview and chart abstraction. Children will be seen for a study-specific visit at enrollment and every three months by study staff. Study visits will be scheduled to coincide with routine health services visits to the child as much as possible.

At each study visit, the study nurse will obtain interim clinical history (e.g., medical/HIV history and CD4 count and, for children on treatment, ART history, current regimen, and adherence questionnaire) by caregiver interview and abstraction of clinical and laboratory data from medical records and record on study data collection tools. Clinic visit attendance and pharmacy drug pick-up for children receiving ART will be obtained by chart abstraction. Blood will be drawn from the HIV-positive children on ART for study viral load testing at enrollment and at 6, 12, and 18 months on study. HIV-positive children not on ART at enrollment who initiate ART during study follow-up will have viral load testing at ART initiation and every six months during the study. Table 3 shows the proposed schedule of data collection.

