**VIII. TIMELINE**

| **ACTIVITY** | **Q2**  **16** | **Q3**  **16** | **Q4**  **16** | **Q1**  **17** | **Q2**  **17** | **Q3**  **17** | **Q4**  **17** | **Q1**  **18** | **Q2**  **18** | **Q3**  **18** | **Q4**  **18** | **Q1**  **19** | **Q2**  **19** |
| --- | --- | --- | --- | --- | --- | --- | --- | --- | --- | --- | --- | --- | --- |
| Protocol and data tools development | X | X |  |  |  |  |  |  |  |  |  |  |  |
| Population Council protocol review |  | X |  |  |  |  |  |  |  |  |  |  |  |
| Protocol submission to IRBs |  |  | X |  |  |  |  |  |  |  |  |  |  |
| Intervention and Study SOP development | X | X | X |  |  |  |  |  |  |  |  |  |  |
| Study training |  |  | X |  |  |  |  |  |  |  |  |  |  |
| Study enrollment |  |  |  |  | X | X | X |  |  |  |  |  |  |
| Qualitative data collection |  |  |  |  |  |  |  |  |  | X | X |  |  |
| Study follow-up |  |  |  |  | X | X | X | X | X | X | X | X |  |
| Data cleaning, analysis |  |  |  |  |  |  |  | X |  |  |  |  | X |
| Presentation of results |  |  |  |  |  |  |  | X |  |  |  |  | X |
| Final results and dissemination |  |  |  |  |  |  |  |  |  |  |  |  | X |

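### The timeline ends follow-up in Q1 2019, one quarter before children enrolled in Q4 2017 reach month 18, and the protocol gives two accrual lengths (9 and 12 months)

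*Protocol*

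**What the plan says.** **Follow-up per child.** The Summary of Proposed Research says: "Each child will be followed for 18 months following enrollment".

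**Endpoint.** The Primary objectives place both primary endpoints, undetectable viral load and HIV RNA above 1,000 copies/mL, 18 months after enrolment. Sample size estimation repeats this, naming viral suppression and "the proportion with HIV RNA >1,000 copies/mL at 18 months". Study Procedures schedules "study viral load testing at enrollment and at 6, 12, and 18 months on study" for children on ART, and Table 5 has a month-18 viral load column.

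**Accrual length in the text.** Below Table 4: "Assuming 10% loss to follow-up, we plan to enroll 444 HIV-positive children receiving ART from unique family units into the study over 12 months".

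**Calendar.** Section VIII (Timeline) has 13 quarterly columns, Q2 2016 to Q2 2019. Its enrolment row reads "Study enrollment | | | | | X | X | X", which is Q2, Q3 and Q4 2017. Its follow-up row reads "Study follow-up | | | | | X | X | X | X | X | X | X | X", which is Q2 2017 to Q1 2019, with the Q2 2019 cell blank. Q2 2019 is marked only for data cleaning and analysis, presentation of results, and final dissemination.

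**The concern.** The calendar and the follow-up rule cannot both be met. A child enrolled on the first day of Q4 2017 reaches month 18 on the first day of Q2 2019, after the last charted follow-up quarter, so the whole Q4 2017 intake is affected and not only its tail. The 12-month accrual in the text makes the mismatch larger.

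The primary endpoints are measured at month 18 and nowhere else, and no month-18 visit window is given that would close a gap of up to one quarter. The sample size has almost no slack: 444 × 0.9 = about 400, against 398 required. The 10% allowance is for loss to follow-up over 18 months; it does not provide for follow-up that stops by the calendar. Children who enrol last may also differ from those who enrol first, because children are enrolled as they are seen in clinic. That is an inference; the protocol does not say so.

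**Working it through.** **1. The plan's own figure.** Inputs from Table 3: control suppression 80%, FAM-CARE 90%, alpha 0.05 (two-sided), power 80%. The pooled-variance formula without continuity correction is

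n = [1.96 × √(2 × 0.85 × 0.15) + 0.842 × √(0.80 × 0.20 + 0.90 × 0.10)]² / 0.10² = 198.96, rounded up to 199 per arm, 398 in total.

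The 10% loss allowance gives 199 / 0.9 = 221.1, rounded up to 222 per arm, 444 in total. Both match the protocol.

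**2. Quarter count.** Add 18 months (six quarters) to each enrolment quarter in the Timeline.

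| Enrolled | Reaches month 18 | Follow-up marked? |
| --- | --- | --- |
| Q2 2017 | Q4 2018 | yes |
| Q3 2017 | Q1 2019 | yes |
| Q4 2017 | Q2 2019 | no |

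Equivalently, 9 months of accrual plus 18 months of follow-up needs 27 months, and the chart gives 8 × 3 = 24. It is one quarter short. With the 12-month accrual from the sample size text, starting in Q2 2017, the need is 12 + 18 = 30 months, through Q3 2019. That is two quarters short and beyond the last column of the chart.

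**3. Share without a month-18 value if the chart is followed.** The protocol states no accrual rate, so the accrual pattern is an assumption. On the charted 9 months:

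- Even accrual from the start of Q2 2017: 3/9 = 33%, or 148 of 444.
- Accrual declining linearly to zero at the end of Q4 2017: (3/9)² = 11%, or about 49 of 444.
- Even accrual that starts only at the end of Q2 2017: 3/6 = 50%.

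**4. Evaluable children and power** (80% versus 90%, two-sided 0.05, clustering ignored). With n per arm,

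power = Φ{[0.10 × √n − 1.96 × √(2 × 0.85 × 0.15)] / √(0.16 + 0.09)}.

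| Pattern on 9 months | Evaluable per arm after 10% loss | Power |
| --- | --- | --- |
| As designed | 199 | 80% |
| Linearly declining | 444 × 8/9 × 0.9 / 2 = about 178 | about 75% |
| Even from start of Q2 2017 | 444 × 2/3 × 0.9 / 2 = about 133 | about 63% |

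**5. Sensitivity to the analysis set.** The Study sampling procedures section says that all enrolled children enter the analysis, with family correlation adjusted for. Of about 666 enrolled, 15% are assumed not to be on ART at entry, leaving 666 × 0.85 = about 566. Then 566 × 2/3 × 0.9 / 2 = about 170 per arm gives power of about 73%, and 566 × 8/9 × 0.9 / 2 = about 226 per arm gives about 85%. These are upper figures, since sibling and facility correlation are ignored.

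**The case against.** The strongest reply is that the Timeline is a quarterly planning chart. The protocol sets no closing date, common cut-off or administrative censoring rule, and the operative text gives every child 18 months and a month-18 draw. Sites that follow the text lose nobody. This stands, and it makes the loss conditional. It does not remove the contradiction: the chart is the only calendar in the document, and it puts final results in the quarter when the last month-18 samples would still be due.

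A reader might infer that a third to a half of the cohort cannot supply the primary endpoint. The documents do not support that. The half (222 of 444 under even accrual) comes from a hybrid schedule that takes the 12 months from the sample size text and the dates from the Timeline, while the Timeline itself stops enrolment at Q4 2017. The third assumes even accrual, which is not stated. Early, front-loaded accrual is plausible: Table 2 lists 575 control and 621 intervention children already on ART at the study facilities, pediatric patients are generally seen monthly, and all eligible children seen are enrolled until the target is met. A late start within Q2 2017 would push the share up, so the uncertainty runs both ways.

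The power figures on the 444 basis may also be pessimistic, because the analysis is to include all enrolled children. This too stands, as step 5 of the working shows.

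**Conclusion.** The point holds as a contradiction between the Timeline and the 18-month follow-up requirement, together with two different accrual lengths. The quarter count is exact and needs no assumption: follow-up is one quarter short for children enrolled in Q4 2017, and two quarters short if accrual takes 12 months from Q2 2017.

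The consequence is conditional on the chart being followed as drawn. In that case, about 11% to 33% of children would lack the primary endpoint on the charted 9 months, with more if enrolment starts late in Q2 2017. Power for 80% versus 90% would be about 75% to 63% on the 444-child basis with 10% loss, and somewhat higher if all enrolled children on ART are analysed. These figures rest on assumed accrual patterns and ignore clustering.

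This is a schedule reconciliation to make before enrolment starts. It is not a flaw in the estimand or the sample size, and the 444 is correctly derived.

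**What to change.** State one accrual length, and use it both in the text below Table 4 and in the Timeline. Then do one of the following:

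- Extend the follow-up row through Q2 2019 for 9-month accrual, or through Q3 2019 for 12-month accrual, and move final data cleaning, analysis, presentation and dissemination after it.
- Close enrolment by the end of Q3 2017, so that every child reaches month 18 by the end of Q1 2019.

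The first option costs one to two more quarters of follow-up already required by the text, and a report later by the same amount. The second costs a shorter accrual window, with the risk of not reaching 444 unique-family children in it. Neither adds a study procedure or changes the sample size calculation.
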